## Abstract

**Background:**

The transitional period from hospital to home is vital for stroke patients, but it poses serious challenges. Good self-management ability can optimize disease outcomes. However, stroke patients in China have a low level of self-management ability during the transitional period, and a lack of effective support may be the reason. With the rapid development of technology, using wearable monitors to achieve real-time and individualized support may be the key to solving this problem. This study uses a randomized controlled trial design to assess the efficacy of using wearable technology to realize real-time and individualized self-management support in stroke patients’ self-management behavior during the transitional period following discharge from hospital.

**Methods:**

This parallel-group randomized controlled trial will be conducted in two hospitals and patients’ homes. A total of 183 adult stroke patients will be enrolled in the study and randomly assigned to three groups in a 1:1:1 ratio. The smartwatch intervention group (*n* = 61) will receive Real-time and Individualized Self-management Support (RISS) program + routine care, the wristband group (*n* = 61) will wear a fitness tracker (self-monitoring) + routine care, and the control group (*n* = 61) will receive routine stroke care. The intervention will last for 6 months. The primary outcomes are neurological function status, self-management behavior, quality of life, biochemical indicators, recurrence rate, and unplanned readmission rate. Secondary outcomes are resilience, patient activation, psychological status, and caregiver assessments. The analysis is intention-to-treat. The intervention effect will be evaluated at baseline (T0), 2 months after discharge (T1), 3 months after discharge (T2), and 6 months after discharge (T3).

**Discussion:**

The cloud platform designed in this study not only has the function of real-time recording but also can push timely solutions when patients have abnormal conditions, as well as early warnings or alarms. This study could also potentially help patients develop good self-management habits through resilience theory, wearable devices, and individualized problem–solution library of self-management which can lay the foundation for long-term maintenance and continuous improvement of good self-management behavior in the future.

**Trial registration:**

The ethics approval has been granted by the Ethics Committee of West China Hospital, Sichuan University (2022–941). All patients will be informed of the study details and sign a written informed consent form before enrollment. The research results will be reported in conferences and peer-reviewed publications. The trial registration number is ChiCTR2300070384. Registered on 11 April 2023.

**Supplementary Information:**

The online version contains supplementary material available at 10.1186/s13063-023-07475-x.

## Introduction

Stroke has become one of the major diseases endangering the health of individuals around the world, with the characteristics of high incidence, high disability rate, high mortality, and high recurrence rate. It is the third most deadly disease in Western countries [1], and it is also the leading cause of death and disability in Chinese adults [2]. With the rapidly aging population in China, the burden of stroke disease presents an explosive growth trend [2, 3].

The transition period from hospital to home is a very important part of disease care for stroke patients after discharge, but it faces severe challenges such as decreased self-care ability, lack of knowledge, poor treatment compliance, and lack of adequate follow-up support and service continuity, which leads to the increased risk of early readmission after discharge and endangers the safety of patients [4–6]. There are two major health tasks in the transition period of stroke patients. The first is functional rehabilitation, including rehabilitation exercise, drug therapy, diet management, and emotional management. The second is to prevent recurrence [7, 8]. These tasks are closely related to patients’ self-management behaviors. The better patients control their self-management behavior, the better their outcome indicators in terms of neurological recovery, ability to perform activities of daily living, and social ability [9]. However, studies have shown that the self-management ability of Chinese stroke patients remains at a lower-moderate level [10, 11]. Lack of effective support is the main reason [12]. With the rapid development of wearable technology, real-time and accurate self-management support using wearable technology may be the key to solving this problem [13, 14]. However, we found that the functions of wearable devices involved in stroke research were mainly intelligent rehabilitation training devices, and they were mostly used for rehabilitation treatment, mainly focusing on the recovery training of limb function [15], sensory stimulation [16], swallowing function [17], and support for cognitive impairment [18]. There were relatively few studies on the monitoring of physical indicators (such as heart rate, blood pressure, electrocardiogram, sleep) and self-management behaviors (such as exercise, medication behavior, diet management) of stroke patients. As a disease with a high disability rate and high recurrence rate, how to combine wearable devices with disease monitoring and health behavior promotion is worthy of further exploration by researchers. There are various types of wearable devices, and with the development of sensors, integrated chips, and intelligent interaction technology, the measurement speed and accuracy of wearable devices are being perfected. Common wearable devices used for stroke include smart insoles [19], leg assist devices [15], rehabilitation sportswear [20], arm bands [21], smart gloves [22], sleeve covers [23], and smart bracelets [24]. Most wearable devices used for disease monitoring are smart bracelets and watches, which are more easily accepted by patients because of their portability and affordability. In sum, most studies take the functional recovery of a certain body part as the outcome index, and few studies focus on the overall well-being of patients and how wearable devices can help them achieve accurate physical and mental care.

Transition management refers to a series of planned behaviors taken to ensure the coordination and continuity of healthcare services when patients are transferred between different healthcare institutions or different healthcare departments in the same institution [25]. In terms of research on self-management interventions for stroke patients during the transition period, most studies have used rehabilitation training, health education, and disease monitoring as the main intervention measures [26, 27]. There is a lack of research on the family environment and community resource utilization. The intervention time ranged from 4 weeks to 9 months, and the intervention intensity gradually decreased over time [28–31]. Intervention strategies included psychological intervention, behavioral intervention, rehabilitation intervention, and treatment compliance. The greater the number of intervention strategies, the greater the impact on patient outcomes [32]. In terms of interventions, multidisciplinary joint intervention is the main method. Compared with a single professional intervention team, a multidisciplinary intervention team can better meet the diverse healthcare needs of stroke patients [33]. In summary, the implementation of the transitional self-management intervention project has achieved certain effects in improving the self-efficacy, quality of life, and treatment compliance and reducing the recurrence rate of patients. However, shortcomings remain: first, the patients’ condition cannot be monitored in real time and accurately after discharge; second, as a disease with a high recurrence rate, it is not possible to effectively warn patients about all possible abnormal conditions. Third, the duration of interventions studied was different, and the timeliness of transition management was ignored. Fourth, universal intervention strategies were adopted for all patients, and individualized intervention measures were not implemented according to the dynamic changes in patients.

Social-ecological resilience (SER) is the ability of individuals to adapt well in the face of adversity and to obtain psychological, social, cultural, and material resources to maintain and restore health. SER includes four levels: individuals, external relationships, community structure, and spirit/culture [34]. For stroke patients, the main difficulties they face are the inconvenience of physical activity caused by neurological deficits, social limitations, increased family dependence, and bad emotions caused by poor recovery, which involve patients’ physiological, psychological, family, and social aspects [35]. Studies have shown that good resilience can effectively promote the self-management ability of stroke patients [36]. The solution-focused approach (SFA) is an important embodiment of resilience theory. It takes finding solutions to problems as the core, focuses on individual advantages, and stimulates the potential ability of patients to solve problems by excavating their own strengths [37]. For chronic disease nursing, the SFA emphasizes that nurses should shift from disease care to helping patients improve adaptability and resilience, stimulating patients’ active participation by exploring their potential and external resources, and ultimately improving patients’ self-management ability [38]. Studies have applied SFA to mental disorders, diabetes, obesity, craniocerebral injury, and other diseases [39–41] and have achieved good results. However, studies on the combination of SAF and wearable technology in the transitional management of stroke patients are rare.

In summary, on the one hand, stroke patients in the transition stage are seriously ill, prone to recurrence, and have poor self-management ability, which requires close monitoring. However, the effect of measures on improving patients’ self-management ability is not ideal, and insufficient support is the bottleneck. On the other hand, wearable technology has been gradually applied in medical research, which has promoted the diagnosis, treatment, and continuous monitoring of diseases. However, there are few reports on how to use wearable technology to provide real-time support for stroke patients who are at home during the transition period and need to pay close attention to changes in their condition. So, how to combine wearable technology in the transition period with real-time support for patients’ self-management is research worthy of further exploration.

## Methods

### Study design

This study is a parallel-group randomized controlled trial with a 1:1:1 randomization scheme that will be conducted in West China Hospital of Sichuan University and Chengdu Second People's Hospital from April 2023 to April 2024. In this study, the Real-time and Individualized Self-management Support (RISS) program will be developed for stroke survivors guided by resilience theory. Patients will wear smartwatches (MLY B10, Huawei wrist electrocardio-blood pressure record) that can collect real-time data such as exercise, sleep, blood pressure, heart rate, and blood oxygen to prompt self-management support for transitional stroke patients. Our hypothesis is that compared with the wristband group and control group, stroke patients who receive the RISS program will have a lower incidence of recurrence rate and an improved quality of life. This study could provide new ideas for increasing patients’ self-management ability, improving quality of life, and optimizing disease outcomes. This trial protocol uses the Standard Protocol Items: Recommendations for Interventional Trials (SPIRIT) reporting guidelines (see Additional file 2). The research method conforms to the joint standard of multiarm test reports. A summary of the study design is shown in Fig. 1. Schedule of enrollment, interventions, and assessments is shown in Fig. 2.

**Fig. 1 Fig1:**
[figure not shown]
The summary of the study design

**Fig. 2 Fig2:**
[figure not shown]
Schedule of enrollment, interventions, and assessments

### Participants

Patients with stroke who are about to be discharged from departments of neurology in the West China Hospital of Sichuan University and Chengdu Second People's Hospital, will be recruited and followed up until week 24 after randomization. Trained investigators and research assistants will approach and inform patients about the study protocol, the randomization process, and the details of the intervention. Participants will sign an informed consent form prior to participation in the study. The inclusion criteria are as follows: (1) meeting the diagnostic criteria of ischemic stroke, confirmed by brain CT or magnetic resonance imaging; (2) stable condition; (3) muscle strength grade II or above, Barthel Index > 40; (4) age ≥ 18 years old; (5) clear consciousness and ability to communicate with researchers through writing/language; (6) residence in Chengdu; (7) discharge home rather than to other care institutions; (8) ability to use a mobile phone and WeChat; and (9) voluntary participation in the study.

The exclusion criteria are as follows: (1) previous history of mental illness or existing mental disorder and (2) serious concomitant diseases, such as severe hepatic and renal insufficiency, severe arrhythmia, frequent angina pectoris, heart failure, and myocardial infarction.

### Recruitment

The recruitment sites for this research are the departments of neurology, West China Hospital of Sichuan University and department of neurology, Chengdu Second People's Hospital. They are all in Chengdu, Sichuan province, China. Each day from 15:00 to 17:00, the research assistants will go to the nurses’ station to collect the basic information of patients who are going to be discharged the next day and screen patients according to the inclusion and exclusion criteria. Then, the research assistants will invite the patients to the nurse station for communication and explain the purpose, significance, specific implementation process, and precautions of the project and invite patients to participate in this study. After obtaining the patient’s consent, the research assistant will record the patient’s basic information (i.e., name, sex, age, disease condition) and contact information and invite patients to join the study’s WeChat group. For the purpose of intention-to-treat analysis, if a participant drops out of the study, the research assistant will also record their basic information and the reasons for withdrawal for comparison with the enrolled participants.

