### Randomization and blinding

Patients who are scheduled to be discharged from the hospital each day will be randomly assigned to the smartwatch intervention group, the wristband group, and the control group at a ratio of 1:1:1. The randomization process is as follows: According to the predetermined number 1 for the smartwatch intervention group, number 2 for the wristband group, and number 3 for the control group, a slip of paper with numbers 1, 2, and 3 will be placed into a sealed, opaque envelope by a research assistant who is unaware of the design of the study. The number selected will determine the group to which the patient will be assigned until 61 subjects are in each group. Because participants in different groups may be in the same hospital room, all participants in the smartwatch intervention group and the wristband group will sign a confidentiality agreement stating that the study will not be disclosed to participants in the control group. Research assistants will generate the allocation sequence and enroll participants, and the researcher will assign interventions.

Because of the nature of the intervention, intervention practitioners cannot be blinded, but patients, data collectors, and statisticians will be blinded to the intervention allocation. In addition, the outcomes of this study will be objectively measured and not influenced by the unblinded intervention. Unblinding will be done after the study.

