### Improving adherence to interventions, modifications, and post-trial care

To improve adherence to interventions in each intervention, we repeatedly emphasized the importance of wearing smartwatches to monitor physical signs for patients’ recovery. And the study required patients to upload self-management logs to the cloud platform every other day. The system will have a built-in reminder module to remind patients through WeChat and mobile phone messages. As a reward, patients who upload their reflection logs on time each week will receive a small gift. This study focuses on health education. The medical treatment or rehabilitation methods of patients in the home stage are based on the doctor’s advice, and the study does not involve additional or alternative medical treatment and rehabilitation methods. If the patient has a need during follow-up, the investigator will communicate with the patient’s doctor to provide the patient with a solution to the problem as an alternative treatment or rehabilitation method. After the intervention, the smartwatch will be taken back, but the WeChat group will not be dissolved. Patients can contact the medical staff in the WeChat group for answers if they have any questions.

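### The confidentiality agreement leaves smartwatch-to-wristband disclosure open, and a study WeChat group offered without regard to arm is a possible shared channel during follow-up

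*Protocol article*

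**What the plan says.** **Confidentiality agreement.** The section Randomization and blinding notes that patients of different arms may share a hospital room. For that reason the smartwatch and wristband participants "will sign a confidentiality agreement stating that the study will not be disclosed to participants in the control group". No other direction of disclosure is covered.

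**WeChat group.** WeChat ability is required of every participant: inclusion criterion 8 in the Participants section is "ability to use a mobile phone and WeChat". In the Recruitment section, once consent is obtained, the research assistant records "contact information and invite patients to join the" study's WeChat group. The group is in the singular and arm is not mentioned. Allocation is described only in the section that follows. Under Improving adherence to interventions, modifications, and post-trial care, the smartwatch is taken back after the intervention "but the WeChat group will not be dissolved". The next sentence is "Patients can contact the medical staff in the WeChat group for answers if they have any questions".

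**Contrasts.** The hypothesis in Study design compares RISS with both the wristband group and the control group.

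**Outcomes.** Under Evaluation methods, self-management behaviour (SSBR) and quality of life (SF-12 v2) are primary outcomes, taken from questionnaires that patients complete themselves, or with items read aloud where needed.

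**The concern.** The plan treats exchange between arms as a real threat and adopts a rule against it, but the rule does not match the hypothesis. It shields the control arm and leaves the wristband arm open to disclosure from the smartwatch arm. Part of RISS is information that can be passed on: self-management goals, problem–solution material and individual advice. A wristband patient who receives some of it moves towards the RISS arm, and the RISS-versus-wristband difference shrinks.

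The stated reason for the agreement is the shared ward. Screening takes place the day before discharge, so that exposure is short. A study-wide WeChat group, if it holds all arms, would link the same patients through the 6 months of follow-up. The plan does not mention the group as a contamination route. Self-reported outcomes such as SSBR and SF-12 are where shared advice, or knowledge of what others receive, would most plausibly show.

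**Working it through.** **1. Which disclosure routes the agreement closes**

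| From | To | Covered? |
|---|---|---|
| Smartwatch | Control | Yes |
| Wristband | Control | Yes |
| Smartwatch | Wristband | No |

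The uncovered row is the one that bears on RISS versus wristband. This follows from the agreement's wording and does not depend on how the WeChat group is organised.

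**2. What the text establishes about the WeChat group**

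- Stated: an invitation after consent, undifferentiated by arm, to a group named in the singular; WeChat ability required of everyone; the group still in existence when the watch is returned.
- Inferred: that one group holds all three arms, and that it is in active use during follow-up.
- Not stated: who may post, what is posted, or that RISS content is delivered there.

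**3. The plan's own sample size**

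Inputs from the Sample size section: three groups, alpha 0.05, eta-squared 0.06, 53 per group before loss, 61 after adding 15% (53 × 1.15 = 60.95). The method is one-way ANOVA with a noncentral F distribution.

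- f² = η²/(1 − η²) = 0.06/0.94 = 0.0638, so f = 0.2526.
- With N = 3 × 53 = 159, the noncentrality is 0.0638 × 159 = 10.15 on 2 and 156 degrees of freedom.
- Power at 53 per group is 81.4%, and 80% power needs 52 per group. The plan's 53 is therefore reproduced to within one patient at beta = 0.20.
- The printed beta of 0.02 would need 100 per group, so it does not go with 53. That is a separate matter. The illustration below uses 53 as planned.

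**4. Illustration of dilution**

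Let c be the share of the between-arm effect lost, so that f becomes f(1 − c). The document gives no value for c and makes no explicit allowance for it. The range 0 to 30% is an assumption.

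| c | η² after dilution | Power, 53 per group | Power, 61 per group | n per group for 80% |
|---|---|---|---|---|
| 0 | 0.0600 | 81.4% | 86.8% | 52 |
| 10% | 0.0492 | 72.1% | 78.5% | 64 |
| 20% | 0.0392 | 61.2% | 67.8% | 80 |
| 30% | 0.0303 | 49.3% | 55.5% | 104 |

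The sample-size equivalent is 1/(1 − c)²: 1.23 at 10% and 1.56 at 20%.

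Uniform shrinkage is a simplification. Disclosure from smartwatch to wristband patients alone would narrow RISS versus wristband and leave RISS versus control as it was.

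**The case against.** **Mixing of arms is not stated.** The article says patients are invited, not that all join, and it nowhere says the arms share one chat. The number of chat groups and the posting rules are operational detail that a full protocol may contain. This stands. The WeChat part of the point is conditional, and one clarifying sentence could settle it.

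**Staff answers come after the intervention.** A reader might infer that every patient enters, at consent, a group where staff advise throughout the trial. The sentence on staff answers follows the return of the watch. The intervention lasts 6 months and the last assessment is at 6 months, so on those timings such answers cannot affect a trial outcome. Keeping the group does imply that it existed earlier, but its use during follow-up is not described.

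**RISS is not delivered in the group.** A reader might also infer that comparators can see watch readings and RISS advice there. The text does not support that: readings pass through the app to the platform, solutions are pushed to the phones of the patient and family, and sessions are individual. What remains is patients passing on what they have learned.

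**The agreement limits the channel.** If controls are in the group, a smartwatch patient who posts study content there breaches the agreement. This is a fair point. The open route is then mainly private messages or conversation between smartwatch and wristband patients. Separate chats alone would not close that route, so the agreement must be reworded as well.

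**Blinding.** The plan says "but patients, data collectors, and statisticians will be blinded to the intervention allocation". It is tempting to say that WeChat breaks this. But patients are told the details of the intervention before consent and can see whether they have a watch, a wristband or neither. Patient blinding fails with or without WeChat and adds no weight here.

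**Pairwise figures.** Eta-squared 0.06 can be read as a pairwise difference of 0.54 SD, with Bonferroni-adjusted power of about 64% before any dilution. That value holds only if the wristband and control means are equal; evenly spaced means give 0.62 for RISS–control and 0.31 for RISS–wristband. The shortfall from 81% to 64% also comes from the pairwise target and not from contamination. The omnibus figures are the ones that match the plan's calculation.

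**Conclusion.** The point holds in two parts of unequal strength. The gap in the agreement is explicit: as written, nothing restrains disclosure from smartwatch to wristband patients, although that contrast is half of the hypothesis. The shared WeChat channel is a reasonable reading of the singular wording and the undifferentiated invitation, but it is an inference.

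The likely direction of any effect is towards no difference, mainly on SSBR and SF-12. Its size cannot be known from the document. Under an assumed uniform loss of 10% or 20% of the effect, omnibus power at 53 per group and eta-squared 0.06 would fall from about 81% to 72% or 61%. These figures show sensitivity and are not a forecast. The plan should be changed, because the correction is specific and nearly free and the rule as written leaves a hypothesised contrast unprotected.

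**What to change.** - Invite patients to WeChat only after allocation, into arm-specific groups or one-to-one chats, and keep them separate until the 6-month assessment is complete.
- Reword the agreement so that it bars disclosure to participants of any other arm, not only to controls.
- If the groups are already arm-specific, say so in the Recruitment section. The agreement still needs the change.

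The cost is two extra chat groups and one changed sentence in the agreement. Sample size, assessments and analysis are unaffected.
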